### Sample size

The study requires a total of 2700 smokers newly diagnosed with pulmonary TB (∼43 recruits from 63 TB centres, the clusters) assuming that 20% might not provide primary outcome data. This sample also includes the first 16 participants taking part in the pilot study, in case the intervention needed major refinement then we would be unable to use their data.

The required sample size for the superiority trial (phase 3) was determined by using a power of 90%, a significance level of 5% and expected abstinence rates of 18% for mTB-Tobacco and 8% for normal treatment after 6 months.^13^ The study will comprise a total of 27 TB centres, considering the ratio of intervention to control as 2:1. After considering a 20% attrition rate, it was determined that the sample size would be 704 participants. This would result in an average of around 26 individuals in each cluster. Given that the study will be carried out as a cRCT with an intracluster correlation coefficient of 0.02,^19^ the design effect was computed to be 1.50. This results in an effective sample size of around 1080 people (or 40 subjects per site).

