In the non-inferiority trial (phase 4), considering 90% power, one-sided hypothesis and 2.5% significance level to establish non-inferiority of mTB-Tobacco intervention to face-to-face behavioural support, comparing 18 clusters in each treatment arm assuming face-to-face achieved 18% abstinence at 6 months and the non-inferiority margin was 8%. Assuming that just 2% would give up with no intervention at all, the established treatment effect of face-to-face behaviour support over natural cessation over 6 months would then be 16% (18–2%). The non-inferiority margin of 8% equates to the mTB-Tobacco intervention preserving at least 50% (8/16) of the established treatment effect of the face-to-face intervention. The above-mentioned sample size assumptions will be checked midway through the recruitment period, and the sample size will be adjusted accordingly. Considering a 20% attrition rate, the final sample size was determined to be 1036 participants, resulting in approximately 29 participants per cluster across 36 clusters (18 in each arm). The design effect was calculated to be 1.56, yielding an effective sample size of approximately 1620 subjects (or 45 subjects for each site). Further adjustments to the sample size assumptions will be made midway through the recruitment period as needed. Sample size details for superiority and non-inferiority trials are given as online supplemental figure 1.

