#### Cost-effectiveness analysis

Health economic evaluation will be conducted to establish the value for money afforded by the mTB-Tobacco intervention. The cost of providing the interventions will be recorded and calculated using local cost data. Costs include staff, premises and pharmaceutical products. Patients’ wider use of public and private healthcare will also be recorded, using a self-report service use questionnaire. Patient cost profiles will be calculated by applying country-specific unit cost tariffs to quantities. Total intervention cost, costs of wider healthcare use and also patients’ out-of-pocket expenditure will be derived, and a total cost will be applied to each patient in each trial arm.

In the superiority trial (phase 3), an incremental cost-effectiveness analysis (CEA) of the mTB-Tobacco intervention will be conducted, over and above usual care. European Quality of Life 5-dimensions 5-levels (EQ-5D-5L) questionnaire will be used to calculate quality-adjusted life years (QALYs) using the area under the curve.^21^ Incremental cost-effectiveness ratios (ICERs) will be presented in terms of (1) cost per QALY and (2) cost per additional quitter as based on the secondary outcome of the trial. A 12-month time horizon is selected for the CEA to use the longer-term window of healthcare use and changes in health-related quality of life. A full sensitivity analysis will be presented to assess the robustness of the results and the probability that mTB-Tobacco intervention is cost-effective at a range of threshold values.

In a non-inferiority trial (phase 4), resource quantities and attribute unit costs will be recorded for the mTB-Tobacco intervention and face-to-face behaviour support, inclusive of wider health system costs following the methodology of the phase 3 superiority trial. Costs for each arm will be calculated and compared with a predefined acceptable cost difference. A CEA will also be done for the non-inferiority trial (phase 4). Differences in costs and QALYs between treatment arms will be estimated to calculate the ICER for the cost per QALY and cost per additional quitter.

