Underlying uncertainty around the decision to adopt the intervention will be assessed using non-parametric bootstrap resampling technique. Bootstrapping is an efficient method for calculating the confidence limits for the ICER as its validity does not depend on any specific form of underlying distribution. We will perform the bootstrap 5000 replications and construct the 95% CIs for the ICERs based on the bootstrapping results. Cost-effectiveness acceptability curves^22^ will be constructed based on the bootstrap iterations to estimate the probability that the intervention is cost-effective at different threshold values for one QALY.

The ICER, calculated in terms of the cost per QALY, will be used to assess the value of money afforded by the intervention over and above the control and draw conclusions with respect to the potential cost-effectiveness of the intervention. To assess the impact of imputing missing data, we will also conduct a complete case analysis based on the participants who have both complete costs and QALYs at all time points, following the same analysis method as the primary analysis above. Sensitivity analyses using pattern mixture modelling will be used to examine the assumptions for multiple imputation methods.

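### In phase 4 the planned bootstrap confidence intervals for the ICERs would be uninterpretable, because the effect difference in the denominator is expected to lie near zero

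*Protocol article*

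**What the plan says.** In the protocol article, the Cost-effectiveness analysis section plans two things for phase 4. Costs per arm are to be compared with an acceptable cost difference fixed in advance. A cost-effectiveness analysis is also planned: "Differences in costs and QALYs between treatment arms will be estimated to calculate the ICER", for cost per QALY and cost per additional quitter.

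The text on uncertainty follows the descriptions of both phases and excepts neither: "We will perform the bootstrap 5000 replications and construct the 95% CIs for the ICERs based on the bootstrapping results". The reason given is that the bootstrap needs no particular underlying distribution to be valid. Acceptability curves are to be drawn from the same replicates, over thresholds for one QALY. The section closes by making the cost-per-QALY ICER the quantity from which conclusions on cost-effectiveness are drawn.

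Under Sample size, phase 4 is planned "assuming face-to-face achieved 18% abstinence at 6 months and the non-inferiority margin was 8" percentage points. No phase 4 rate for mTB-Tobacco is stated. The only one given is for phase 3: "expected abstinence rates of 18% for mTB-Tobacco and 8% for normal treatment after 6 months".

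**The concern.** An ICER divides a cost difference by an effect difference. Phase 4 asks whether mTB-Tobacco is about as good as face-to-face support, so the denominator is expected near zero and the replicates fall on both sides of it.

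Take differences as mTB-Tobacco minus face-to-face, with mTB-Tobacco cheaper. A replicate in which it is also better gives a negative ratio. A replicate in which it is worse gives a positive ratio, the same sign as dearer and better. The replicates nearest to no effect give the most extreme ratios, of either sign. Percentiles of such a mixture do not order replicates from favourable to unfavourable.

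Resampling removes the need to assume a distribution, but it does not make a ratio well behaved when its denominator straddles zero. The stated justification therefore fails in the very result that the non-inferiority phase hopes for: similar abstinence at lower cost.

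**Working it through.** **1. What effect difference was phase 4 planned on?** Inputs (Sample size): 18% for face-to-face, margin 8 points, one-sided 2.5%, power 90%, attrition 20%, 1036 participants before the design effect. With mTB-Tobacco also at 18%, n per arm = (z_alpha + z_beta)² × 2 × 0.18 × 0.82 / 0.08².
- At the stated 90% power: 485 per arm, 970 in total, 970/0.8 = 1213. This does not reproduce 1036.
- At 85% power: 414.1 per arm, 414.1/0.8 = 518 after rounding up, 1036 in total. This reproduces it.
- Keeping 90% power and solving for the difference d, with (0.08 + d)² in the denominator and mTB-Tobacco at 0.18 + d: d = 0.0072, or +0.7 points, also gives 518 per arm.

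So 1036 is consistent with a planned difference of 0 to +0.7 points. The mismatch with 90% power is a separate matter, used here only to infer that difference. The next step of the plan does reproduce: 1 + 28 × 0.02 = 1.56; 1036 × 1.56 = 1616, rounded to 36 × 45 = 1620.

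**2. Standard error of the abstinence difference.**
- Analysed per arm: 1620 × 0.8 / 2 = 648, or 36 per cluster.
- Design effect at 36 per cluster, with the ICC of 0.02 stated for phase 3: 1 + 35 × 0.02 = 1.70.
- Effective n per arm: 648/1.70 = 381.
- SE = sqrt(2 × 0.18 × 0.82 / 381) = 0.0278. For design effects from 1.56 to 1.88 it is 0.0267 to 0.0293.

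**3. Share of replicates with a negative denominator**, Phi(−d/SE), when the observed difference equals d:

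| d (points) | Share negative |
|---|---|
| 0 | 50% |
| +0.7 | 40% |
| +2 | 24% |
| +3 | 14% |

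At d = 0 the share is 50% whatever the SE.

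**4. What the interval looks like.** The article gives no cost difference, so these values are assumed, in arbitrary currency units: observed effect difference 0, SE 0.0278, 5000 draws, costs and effects independent.

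| Cost difference (SE) | 2.5 to 97.5 percentile of cost per quitter |
|---|---|
| −1 (1) | −731 to +648 |
| −5 (1) | −3315 to +2899 |
| −20 (5) | −11204 to +12753 |

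For −5 (1), 50% of replicates are cheaper and better and 50% cheaper and worse. With four other seeds the lower limit ran from −3055 to −2485 and the upper from +2702 to +3186. The limits scale with the assumed cost; the change of sign comes from the denominator alone.

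**5. The same situation as net benefit.** With cost difference −5 (SE 1) and threshold L per quitter, net benefit = L × 0 + 5 and SE = sqrt((L × 0.0278)² + 1²).
- L = 100: SE 2.96, so 5 ± 1.96 × 2.96 = −0.8 to 10.8; 95% of simulated replicates are positive.
- L = 500: SE about 13.9, so about −22 to 32; 63% are positive.

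These summaries are finite and ordered.

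**6. Contrast with phase 3 cost per quitter.** At 18% v 8%, 1080 enrolled, 20% attrition and design effect 1 + 31 × 0.02 = 1.62, the SE is 0.0288 and Phi(−0.10/0.0288) is about 0.03%. The denominator is safely positive at the design effect.

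**The case against.** The case on the other side has several parts.

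- **The phase 4 economic result is more than this interval.** This stands. The comparison with an acceptable cost difference needs no denominator, and the acceptability curves remain valid because each point is the share of replicates with positive net benefit. A reader might infer that the whole phase 4 economic analysis is meaningless; the article does not support that. But the curves are defined only for QALYs, and conclusions are assigned to the ICER.
- **Equal abstinence is inferred.** This stands. The 18% for mTB-Tobacco is a phase 3 figure, and equal rates at 90% power do not give 1036. The observed difference may also be larger; the Introduction cites face-to-face quit rates as high as 41%. The result is therefore conditional. It weakens as the difference grows, but 14% of denominators are still negative at +3 points.
- **The interval type is not named**, and a health economics plan may add detail. This stands in part: the unreadable result is that of an ordinary interval on the ratio. The article nevertheless commits to intervals for the ICERs and gives a reason that fails here.
- **Phase 3 might be thought affected too**, through cost per QALY. The article gives no expected QALY difference or spread, so any such figure would rest on invented inputs. The point is confined to phase 4.

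**Conclusion.** The point holds for phase 4. If the abstinence difference is near the implied 0 to +0.7 points, about 40% to 50% of replicates have a negative denominator for cost per additional quitter, and an ordinary bootstrap interval for that ICER cannot be interpreted. A similar problem is likely for cost per QALY if quit rates are similar, but its size cannot be given.

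This rests on an ICC of 0.02, 20% attrition, a normal approximation and the primary-outcome abstinence rates. The article bases the phase 3 quitter ratio on the secondary outcome, for which it gives no planning rate; if quitters are counted that way, the shares and the phase 3 contrast above are only indicative. The currency figures are illustrations only.

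The primary outcome, sample size and stage decision are untouched. What remains is a secondary analysis in which cost per quitter has no valid uncertainty summary and the decision is tied to a ratio that is unstable in the expected scenario.

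**What to change.** For phase 4:
- Replace the confidence intervals for the ICERs with incremental net monetary benefit and its 95% interval at the planned thresholds.
- Report the cost difference and each effect difference with its own 95% interval, and show the cost-effectiveness plane.
- Keep the QALY acceptability curves and add one for cost per quitter.
- Give an ICER as a point estimate only when the effect difference is clearly away from zero.
- Base the conclusion on net benefit and the curves, and limit the statement about bootstrap validity accordingly.

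The cost is small. The same 5000 replicates are summarised differently and no new data are needed. The one addition is a set of threshold values for a quitter, to be stated before the phase 4 data are analysed.

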### Randomisation

Since the interventions will be delivered at the group level, this trial is designed as a cluster cRCT where TB centres will be randomly allocated to the different trial arms. The TB centres (clusters) would be randomised in a 2:2:1 ratio to mTB-Tobacco (intervention A), face-to-face (intervention B), or standard care (Control). An independent statistician, blinded to clusters, will identify and use computer-generated random number lists to generate the allocation sequence. The allocation will be based on using minimisation to ensure balance across the groups on the average number of patients with TB seen per month and geographical locations (Bangladesh and Pakistan).

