#### Inferential statistics

A mixed-effects model will be used to assess the impact of mTB-Tobacco on continuous outcomes, incorporating fixed effects for the intervention, random effects for clusters and relevant covariates. Logistic regression within the mixed-effects framework will be used to analyse categorical outcomes, accounting for cluster-level variability and intervention effects for the analysis of data in this cRCT. At the end of phase 3 superiority trial, an interim analysis will be done by an independent statistician to assess the effectiveness of the mTB-Tobacco intervention. The result will decide whether the trial needs to proceed to phase 4 non-inferiority trial or be terminated early. In this study, the missing data patterns will first be examined to determine whether the missingness adheres to patterns of complete randomness, randomness or non-randomness. Multiple imputation, a robust technique that generates multiple data sets with imputed values for missing observations, will be used to address the missing data. As a sensitivity analysis technique, missing data imputation will be used to evaluate the robustness of our findings.^20^ The estimates of the intervention effect will next be compared between analyses carried out with complete case analysis and analyses using imputed data sets. This will improve the validity of the study’s conclusions by enabling an assessment of the effect of missing data on the estimation of intervention effects in this cRCT. Open-source R Project software and JASP Team (2024; V.0.19.3) computer software will be employed as our primary tools for data analysis.

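### The bootstrap for the ICER intervals and acceptability curves is specified without a resampling unit or any allowance for TB centres; if patients are resampled independently, cost-effectiveness uncertainty will be understated

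*Protocol article*

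**What the plan says.** The Randomisation section makes the TB centre the unit of allocation: "this trial is designed as a cluster cRCT where TB centres will be randomly allocated to the different trial arms". Two other parts of the article act on this. The Inferential statistics section analyses continuous outcomes with a mixed model "incorporating fixed effects for the intervention, random effects for clusters and relevant covariates" and treats categorical outcomes in the same framework. The Sample size section inflates both phases using an "intracluster correlation coefficient of 0.02".

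The Cost-effectiveness analysis section builds its data patient by patient: "a total cost will be applied to each patient in each trial arm". For uncertainty it states: "Underlying uncertainty around the decision to adopt the intervention will be assessed using non-parametric bootstrap resampling technique". The reason offered for choosing the bootstrap is that "its validity does not depend on any specific form of underlying distribution". It then fixes the replicates and the intervals: "We will perform the bootstrap 5000 replications and construct the 95% CIs for the ICERs based on the bootstrapping results". The acceptability curves "will be constructed based on the bootstrap iterations to estimate the probability that the intervention is cost-effective at different threshold values for one QALY".

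No centre, cluster or ICC appears in that section. The resampling unit is not named, and nothing says whether the mixed model for continuous outcomes also covers costs and QALYs.

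**The concern.** A non-parametric bootstrap makes no assumption about the shape of the cost or QALY distribution, but it does need resampling units that are independent. In this trial those units are centres. The reason given in the article deals with shape and is silent on independence, which is the assumption a cluster design breaks.

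If individual patients are drawn with replacement within arm, the replicates do not carry the between-centre variation. At any positive ICC the error runs one way: the intervals are too short and the acceptability curves too steep. Using the centre random-effects model for the point estimates would not cure this if the bootstrap around it still drew patients one at a time.

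Cost-effectiveness is a stated aim alongside effectiveness. The article intends to judge value for money from the cost per QALY, so overstated certainty would feed directly into adoption decisions.

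**Working it through.** **Inputs from the Sample size section.** ICC 0.02 (abstinence). Phase 3: 27 centres at 2:1, so 18 intervention and 9 control; about 26 patients per centre before inflation and 40 after. Phase 4: 18 centres per arm; about 29 per centre before inflation and 45 after. Attrition 20%.

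**The plan's own figures.** Design effect DE = 1 + (m − 1) × ICC.
- Phase 3: 1 + 25 × 0.02 = 1.50, as stated.
- Phase 4: 1 + 28 × 0.02 = 1.56, as stated.

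**Cluster sizes for the economic data.** I assume the 20% attrition also applies to costs and QALYs.
- Phase 3: 40 × 0.8 = 32.
- Phase 4: 45 × 0.8 = 36.

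These sizes differ from those behind 1.50 and 1.56, so the design effects below differ too.

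**Effect of ignoring centres.** The standard error is too small by a factor 1/√DE. A nominal 95% interval then has coverage 2Φ(1.96/√DE) − 1. This holds for an approximately normal mean difference or net benefit.

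| Phase | m | Assumed ICC | DE | Interval should be wider by | Coverage |
|---|---|---|---|---|---|
| 3 | 32 | 0.01 | 1.31 | 1.14 | 91.3% |
| 3 | 32 | 0.02 | 1.62 | 1.27 | 87.6% |
| 3 | 32 | 0.05 | 2.55 | 1.60 | 78.0% |
| 4 | 36 | 0.02 | 1.70 | 1.30 | 86.7% |

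Cluster size matters less than the ICC. At ICC 0.02 in phase 3, m = 26 gives 89.0% and m = 40 gives 85.8%.

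**Acceptability curve.** A naive probability p corresponds to Φ(z_p/√DE). With p = 0.95 and m = 32, this is 0.925 at ICC 0.01, 0.90 at 0.02 and 0.85 at 0.05.

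**Simulation check.** One normal outcome, 18 v 9 centres of 32, 400 trials with 400 resamples each, so coverage is good to about ±3 points.
- ICC 0.02: the true standard error was 0.086. The patient bootstrap gave 0.072 and 88% coverage; the centre bootstrap gave 0.086 and 92%.
- ICC 0.05: coverage was 78% for the patient bootstrap and 92.5% for the centre bootstrap.

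The centre bootstrap removes most of the shortfall but stays a little below 95% with so few centres.

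**The case against.** A reader might infer that the plan fixes an ordinary patient-level bootstrap and that its intervals will therefore be wrong. The article does not support that. It never uses those terms, and a bootstrap that draws whole centres, or centres and then patients, is also non-parametric and would comply with the sentence as written. Recording one cost per patient settles nothing either, since a centre-level bootstrap needs the same data. The article presents itself as a structured account of the approved protocol, so the full protocol or a health economics plan may name the unit. The random-effects model for continuous outcomes might be meant to cover costs and QALYs. All of this stands, and it makes the conclusion conditional.

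A reader might also infer that costs cluster more strongly than abstinence because unit costs are shared within a centre. The article points the other way on unit costs: wider healthcare use is priced from tariffs set by country, and country is a minimisation factor. Service use could still vary by centre, but nothing shows that the ICC for costs exceeds 0.02.

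What does not stand is that this is mere condensation. The section gives the number of replications, a complete-case analysis and pattern mixture modelling, and it argues for the validity of the bootstrap. That argument leaves out the one assumption the design violates, while the clinical analysis and the sample size both deal with it.

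**Conclusion.** The point holds in conditional form. The bootstrap is specified and justified without a resampling unit and without regard to centres, in a trial that randomises centres and models them elsewhere. If patients are resampled independently, nominal 95% coverage in phase 3 falls to somewhere between about 91% and 78%, with 88% at ICC 0.02; in phase 4 it is about 87% at ICC 0.02.

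The size rests on three assumptions: an ICC for costs and QALYs that the article does not give, the same 20% loss for economic data as for the primary outcome, and a normal approximation for a mean difference or net benefit in place of the ICER itself. The direction does not depend on the particular ICC, provided it is positive. If the full protocol or an economic plan already resamples centres, only the description needs correcting.

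**What to change.** State in the cost-effectiveness section that the bootstrap resamples TB centres within arm, stratified by country, keeping each patient's cost and QALY as a pair, and that the same replicates produce both the ICER intervals and the acceptability curves.

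Phase 3 has only 9 control centres, so a plain centre bootstrap is likely to under-cover slightly. Specify a small-sample-adjusted version, for example a two-stage bootstrap with shrinkage, or a bivariate multilevel model for cost and QALY with a centre effect. Either is acceptable; the choice should be made before the phase 3 economic data are analysed. Reporting the estimated ICCs for costs and QALYs would show how much the clustering mattered.

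No new data are needed. The cost is modest extra analysis work, more for the bivariate model than for the bootstrap, and wider intervals.
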